### Randomization and allocation

2.2

Randomization in the study is conducted as *stratified block randomization* with four strata and a block size of four. The strata are defined according to dyslexia risk status and infant gender as follows: dyslexia-risk boys, dyslexia-risk girls, no-risk boys, and no-risk girls [as dyslexia risk and infant gender are expected to have a large effect on the primary outcome measures, e.g., Snowling and Melby-Lervåg, 2016].

For each stratum, block randomization is completed by randomly permuting a list of four-letter combinations consisting of AABB, where A = experimental arm (music intervention) and B = control arm (circus intervention), in order to reach balanced group sizes in the two arms. This also ensures that new music and circus intervention groups can be started at the same time, as new participants will be randomized to the two arms at a similar pace during recruitment. Author PV produced the randomization sequence by creating a list of 200 random permutations of AABB with MATLAB v. R2023a at the onset of participant enrollment, and chronologically labeled them according to block (1, 2, 3…50) and stratum (a, b, c, d); however, this randomization sequence is not concealed from the trial coordinator who assigns the participants to the intervention arms. The trial coordinator is advised to enroll new participants and assign them to the intervention arms in the order that they are successfully screened for eligibility and express oral consent. In situations where there are more such families than available spots in the intervention groups or the strata have large differences in sample sizes (> 10 infants), the trial coordinator is advised to first enroll participants in the strata with smaller sample sizes and to start enrollment from participants who help to balance the mean age of that stratum close to 10 months of age.

Blindness of the researchers to the randomization has been ensured by assigning a dedicated member of the research team as trial coordinator. The trial coordinator screens participants for eligibility and assigns them to the two intervention arms according to the randomization sequence. When the evaluation of dyslexia risk has to be conducted, the trial coordinator will assign the evaluation to one of the outcome assessors, and that assessor will not participate in future outcome assessments for that family (as their blindness to the participant’s dyslexia risk status has been violated). The trial coordinator will not act as an outcome assessor or intervention instructor and will keep track of any blindness violations.

Blindness of the participants to the trial design is ensured by presenting the study as evaluating the effect of early-age hobbies on language development, without either intervention being a control arm. To evaluate how successful this was, participating families are queried about their expectations regarding the benefits of the two intervention arms on the primary outcome measures (see Supplementary material).

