### Trial design and hypotheses

1.3

This randomized controlled trial is conducted as a double-blind, two-arm parallel assignment design with the primary purpose of treatment, with primary and secondary outcomes assessed at baseline, post-intervention, and at follow-up approximately 1.5 years from baseline. The experimental arm will receive family music training (music intervention), and the control arm will receive family circus training (circus intervention). The study framework is a superiority trial with greater expected benefits from the experimental than the control arm. All participants are randomized to one of two interventions with a 50:50 allocation ratio, both consisting of approximately 6 months of weekly group sessions together with a parent (Figure 1: study flowchart).

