### Outcomes

2.5

Outcomes of the trial are evaluated with three assessment points: at baseline (before intervention), post-intervention (six months from baseline, end of intervention), and follow-up (1.5 years from baseline). Data collection carried out by the outcome assessors takes place at the University of Helsinki research laboratories. Outcome assessors are trained graduate students in psychology and speech and language pathology, supervised by a licensed clinical psychologist (PV, in collaboration with a licensed speech and language pathologist, SS). All questionnaire data are collected online via REDCap (Research Electronic Data Capture).

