### Data management

2.7

The data involve digital and paper format data and biological samples. All digital data are stored on a University of Helsinki network drive in a group folder accessible only to the research group members and backed up by the university’s IT center. Digital data are stored in password-protected relational databases where they are transferred directly from the REDCap (questionnaires) or entered manually by the outcome assessors (behavioral test scores, EEG measurement protocols). All paper form data and biological samples are stored in locked premises and locked cabinets that can only be accessed by essential personnel of the research team. A collaborating laboratory (Folkhälsan Research Centre) will store the biological samples (saliva samples) and send them in pseudonymized form (without direct identifiers) to another laboratory for genetic laboratory analysis (DNA sequencing and targeted genotyping; procured as a contracted service); remaining samples will be returned to the collaborating laboratory for long-term storage (see below).

Data pseudonymization is performed during data collection, and all data analysis is conducted without direct identifiers. Direct identifiers are replaced by codes and stored separately in password-protected files. The passwords are only available to research team members who essentially need the information (e.g., contact information of the parents is only accessible to outcome assessors and the trial coordinator). Only the trial coordinator and, as a safety procedure, author PV, have direct access to the separate password-protected files that contain information on the arm allocation of the participants. This information will be included in the password-protected relational databases together with the rest of the digital data but in an indirect manner, so that it cannot be revealed accidentally. Personal information and all records of interested families not enrolled in the study will be destroyed by the trial coordinator by the end of participant recruitment.

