### Risk assessment and monitoring

2.8

Participation in the interventions is expected to have no adverse effects on the health, wellbeing, or safety of the participating families. Therefore, a data monitoring committee has not been appointed. Nevertheless, intervention instructors are asked to report all negative occurrences in their intervention groups after each session, including, for example, minor accidents, crying or negative emotions, and conflicts between the participants (see Supplementary material). Additionally, all negative feedback or concerns raised by the parents that the intervention instructors, researchers, outcome assessors, or trial coordinator receive during the trial will be collected and stored by the trial coordinator.

Challenges in participant recruitment or attrition are expected to be minor, particularly regarding the primary outcomes (evaluated directly before and after the intervention) for three main reasons. Firstly, participation in the trial is expected to be engaging and rewarding, as pointed out in section 2.1.3. Secondly, several actions are taken to support adherence and commitment to the study, as described in section 2.4. Thirdly, the follow-up period of 1.5 years in total is considered relatively short. Challenges related to data loss are further minimized by using complementary outcome measures. For example, while EEG recordings may not always be successful in infancy and early childhood due to movement artifacts and participant refusal, parental questionnaires will still provide valuable information. Nevertheless, participant drop-outs and no-shows are carefully monitored (see also Supplementary material).

The following measures have been taken to ensure intervention fidelity and arm equivalence. The interventions have been planned in advance, and their execution is based on detailed lesson plans. Teachers are asked to report any deviations from the lesson plan or duration after each lesson. The teachers have planned the lessons together and meet regularly (1 h/month) during the interventions to harmonize their practices as much as possible. The authors PV and BA conduct lesson observations for all teachers. For more information, see Supplementary material.

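### The protocol says the researchers are blind to allocation, but this is not true of the author who supervises the outcome assessors, nor of the second lesson observer

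*Protocol article*

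**What the plan says.** The blinding claim appears in two places in the protocol article. Section 1.3 (Trial design and hypotheses) states: "This randomized controlled trial is conducted as a double-blind, two-arm parallel assignment design". Section 2.2 (Randomization and allocation) states: "Blindness of the researchers to the randomization has been ensured by assigning a dedicated member of the research team as trial coordinator". The same section bars the coordinator from assessing outcomes or teaching classes, and has the coordinator record breaches of blinding. It also says that an assessor who evaluates a family's dyslexia risk does no later outcome assessments for that family.

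Other sections describe what one author, identified by the same initials each time, does in the trial:

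- Section 2.2: this author generated the randomisation sequence.
- Section 2.5 (Outcomes): "Outcome assessors are trained graduate students in psychology and speech and language pathology, supervised by a licensed clinical psychologist". The psychologist is this author, working with a speech and language pathologist.
- Section 2.7 (Data management): this author and the coordinator are the only people who "have direct access to the separate password-protected files that contain information on the arm allocation of the participants". The author's access is described as a safety procedure.
- Section 2.8 (Risk assessment and monitoring): this author and one other author "conduct lesson observations for all teachers".

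**The concern.** A separate coordinator keeps the research team blind only if nobody else on the team learns the arms. Here the person directly above the assessors has several ways to learn them. The coordinator, who also knows the arms, is kept out of assessment; no comparable separation is stated for the supervising author.

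This matters because families cannot be blind to the activity they attend. Section 2.2 claims only that they do not know which arm is the control. The language-ability primary outcomes are parent reports, and section 3.1 (Limitations) concedes that relying on parents alone at baseline is not ideal. It looks to the standardised language test to strengthen what the questionnaires show. That support is worth most if the test is given and scored without knowledge of arm. If a doubtful score or an ERP processing decision is settled by someone who knows the arms, the supporting evidence is less independent than the article says.

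**Working it through.** There is no figure to recompute. The check compares the blinding claim with the roles given elsewhere in the article.

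**Step 1: what the claim could mean.**

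- *Blind to the sequence.* The supervising author produced the sequence, so the claim fails for that author on section 2.2 alone.
- *Blind to families' allocation.* Access to the allocation files (2.7) and lesson observation (2.8) contradict the claim for the supervising author. Lesson observation contradicts it for the second observer too.
- *Only the outcome assessors are meant.* The claim might then be true, but the article does not use the word that way. Section 2.8 lists researchers and outcome assessors as separate groups: "all negative feedback or concerns raised by the parents that the intervention instructors, researchers, outcome assessors, or trial coordinator receive during the trial".

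**Step 2: how much each role reveals.**

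| Role of the supervising author | Section | Reveals a family's arm? |
|---|---|---|
| Generated the sequence | 2.2 | Not alone; the coordinator links families to list positions |
| Can open the allocation files | 2.7 | Potentially, for any participant; actual use is not stated |
| Observes lessons | 2.8 | Yes, for families present; each group is music or circus |
| Supervises the assessors | 2.5 | No; this is where knowledge of arm could reach the outcomes |

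The first three roles are sources of knowledge, of differing strength. The fourth is the link to the outcome data.

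**Step 3: which outcomes are within reach.**

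- CSBS ITC and FinCDI (primary, 2.5.1.1): completed by parents and collected online (2.5), so there is no assessor scoring to influence.
- Speech ERPs and MMRs (primary, 2.5.1.2): quantified from a stated region of interest. The article does not say who takes the processing decisions, so exposure is possible but not shown.
- RDLS-III (secondary, 2.5.2.1) and Bayley motor scale (exploratory, 2.5.3.5): administered by the supervised assessors at 2 of the 3 assessment points, post-intervention and follow-up.

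**Step 4: what can still be protected.** Section 2.6 estimates post-intervention assessments up to March 2026 and follow-up from March 2026 to April 2027. The full follow-up round of both tests therefore falls in the later window.

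**The case against.** The strongest reply is that the people who test the children are graduate students, and no passage shows that any of them knows an arm. The supervising author is not described as testing, scoring or extracting ERPs. File access is openly disclosed as a safety procedure, analysis is done without direct identifiers, and allocation is coded indirectly in the databases to prevent accidental disclosure (2.7). RDLS-III is secondary, its post-intervention scores are already to be read with caution (2.5.2.1), and the Bayley motor scale is exploratory. All of this stands. It limits the point to an overstated claim and an open route, and does not rescue the sentence in section 2.2. Indirect coding guards against accidents; it does not blind someone who can open the files or has watched the class. Supplementary material may add safeguards, but could not make that sentence true as worded.

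Four stronger readings are tempting and should not be drawn:

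- *That assessor blinding has failed.* The harm depends on queries going to the supervising author and knowledge of arm affecting the answers. The article says neither.
- *That the supervising author has seen all 20 groups (10 per arm, 2.6).* Two authors share the observations. The text does not say how they divide the teachers or how many sessions they watch.
- *That parents' complaints unblind assessors.* Section 2.8 covers feedback that anyone happens to receive, and the coordinator already collects it. That a complaint discloses the arm is inference.
- *That withdrawing file access would restore blindness.* It cannot undo what was learned by watching lessons.

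Nor does the article's silence on what follows a recorded breach show that nothing follows; such detail may sit in the full protocol.

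**Conclusion.** The blinding statement in section 2.2 is incorrect as written for two people: the author who supervises the assessors, and the second lesson observer. The contradiction lies in the article's own text and does not depend on anything left to a fuller document.

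Its reach is limited. No assessor is shown to be unblinded, and the parent-reported primary questionnaires are outside it. What is exposed is the supervised RDLS-III and Bayley motor testing, with ERP processing a possibility. The size of any bias cannot be estimated from the article.

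This rests on two assumptions: that the same initials denote the same person throughout, and that an observer of a lesson can see which families attend. The matter should be corrected, because the statement will otherwise be repeated in the trial report and because much assessor-administered testing falls in the follow-up window.

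**What to change.** 1. **Restate the blinding claim.** Section 2.2 should say who is blind to arm (for example, the outcome assessors) and who is not (the coordinator, the supervising author and the second lesson observer). Qualify the double-blind label in section 1.3 to match, and list the supervising author's overlapping roles under Limitations. This costs a few sentences and an entry at the preregistration site, where section 2.1.1 says important modifications are reported.
2. **Redirect queries.** For the remaining post-intervention and follow-up assessments, send scoring and ERP-processing queries to the co-supervising speech and language pathologist. First confirm that this person is blind to arm, which the article does not state. Keep the supervising author's access to the allocation files for safety use only, so that the coordinator is not the sole holder.
3. **Extend the reassignment rule.** Section 2.2 already removes an assessor who has evaluated a family's dyslexia risk from that family's later assessments. Apply the same rule to an assessor who learns the family's arm, wherever another assessor is available, and log every exception.

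The changes use people already named in the article. The downside is some assessor rescheduling.

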### Interventions

2.3

Both intervention arms consist of 20 weekly sessions of 45 min, organized at fixed times and locations in fixed groups of 5–10 parent-infant dyads and an experienced instructor. The intervention arms share the general goals of supporting the infants’ holistic development and parent–infant interaction. Additionally, they have arm-specific teaching goals as specified below. The content, structure, and goals of the interventions, as well as intervention instructors, venues, and materials, are described in more detail in the Supplementary material.

#### The experimental arm (music intervention)

2.3.1

The music intervention is planned based on the practices of Finnish early childhood music education and consists of social, structured, and playful group sessions that involve joint singing, playing with musical instruments, and moving to and listening to music. Based on common age-appropriate practices of Finnish early childhood music education, rhythmic exercises such as tapping, clapping, and playing percussion instruments (claves, maracas, etc.) with infants and parents together, as well as joint singing (mostly by parents), are emphasized in the sessions. Their use is supported by previous research, for example, on the benefits of rhythmic exercises on literacy in dyslexic children (Flaugnacco et al., 2015) and on the benefits of vocal music exposure on speech processing (Virtala et al., 2023). The arm-specific aim is to support the development of musical abilities.

#### The control arm (circus intervention)

2.3.2

The circus intervention consists of social, structured, and playful group sessions that involve acrobatics and other age-appropriate motor exercises with the caregiver, familiarizing participants with the art and equipment of circus and acrobatics. The use of music is limited to occasional background music to set the mood and support the lesson theme (see Supplementary material), so that movement is not synchronized with it. The arm-specific aim is to support the development of motor abilities as well as bodily control and awareness.

### Adherence and commitment to the study and concomitant activities

2.4

Participating families are rewarded for their participation in all phases of the study (baseline, post-intervention, and follow-up assessments) with a small book gift and snacks for the infant, and they are compensated for reasonable travel costs to the research laboratory upon request, in order to promote participant retention and complete follow-up. The parents can also receive oral feedback on their infant’s language and motor performance after the post-intervention and follow-up assessments.

Commitment to participate in the intervention sessions is facilitated by offering families a choice regarding the time and location of their intervention group whenever possible (i.e., when several groups in the right intervention arm have available spots at the time when the infant is in the desired age range). This freedom of choice will not affect their arm allocation but can influence which families participate in the morning versus evening groups. As the time of day may potentially influence intervention efficacy, it will be considered in the analyses of the primary outcomes.

During the interventions, the instructors continuously keep track of non-attendances and inform the trial coordinator in case of two or more consecutive no-shows. In this case, the trial coordinator tries to reach the family and encourage them to attend the sessions as often as possible. Discontinuation of the intervention occurs at the participant’s request.

In order to keep track of the reasons for low adherence, parents are asked to inform the intervention instructor of their absence from the sessions and the reason for it. The most common reasons for non-attendance are also queried from the families at the end of their intervention. The aim is to assess primary outcomes from all participants irrespective of intervention adherence (intention-to-treat analysis) and further investigate the effect of adherence on the primary outcomes (see 2.9). For per-protocol analyses (see 2.9), criteria for successful participation are defined based on the number of attended sessions out of a total of 20 and the total attended duration of the intervention (quantified as the period between the first and the last attended session).

During the intervention, the participating families are requested to refrain from concomitant similar activities. This means regular participation in family musical playschool, family circus, as well as acrobatics, dance, and sports classes for infants and toddlers. Participation in such classes is allowed before and after the 6-month intervention, and participation in other concomitant leisure activities (for example, baby swimming classes or classes targeted to the parent where the infants can be present, such as postpartum yoga) is always allowed. All other concomitant care, including interventions (for example, speech therapy), is permitted throughout the entire study and is inquired about from the families in questionnaires (see 2.5.4).

### Outcomes

2.5

Outcomes of the trial are evaluated with three assessment points: at baseline (before intervention), post-intervention (six months from baseline, end of intervention), and follow-up (1.5 years from baseline). Data collection carried out by the outcome assessors takes place at the University of Helsinki research laboratories. Outcome assessors are trained graduate students in psychology and speech and language pathology, supervised by a licensed clinical psychologist (PV, in collaboration with a licensed speech and language pathologist, SS). All questionnaire data are collected online via REDCap (Research Electronic Data Capture).

#### Primary outcomes

2.5.1

As primary outcomes, the children’s language development will be evaluated at baseline and post-intervention. This includes evaluating language abilities with two standardized parental questionnaires (validated parental report instruments) and speech processing with auditory ERPs and MMRs. The parental questionnaires and the neural measures (ERPs and MMRs) are expected to provide complementary information on early speech and language development.

